#### Multiple comparisons

Each of the six individual behaviours will be analysed separately; for each behaviour, we will generate a 95% confidence interval for the effect of the intervention. The 95% confidence interval corresponds to a type 1 error rate of 5%. If we assume that the behaviours are independent, with six separate tests, the probability that one or more is significant at the five percent level is 0.265. Thus the effective type 1 error rate is 26.5% rather than the nominal 5% assumed in the power calculation. However, the probability of two or more tests being significant purely by chance is 0.033. In practice, the behaviours and associated tests are not independent but this figure can be used as a guide. Provided that the intervention is shown to have beneficial effects on at least two of the clinical behaviours this can be regarded as evidence that the proposed method can be used to develop effective interventions.

### Additional planned analyses

#### Secondary trial analysis

For the two prescribing behaviours, we will conduct an interrupted time series (ITS) analysis to investigate monthly changes over time between intervention and control practices, for 12 months prior to the intervention through 12 months post-intervention (accounting to timing of intervention delivery). We will supplement this analysis with relevant QOF data in each practice, using a non-equivalent dependent variables analysis to further bolster the ITS.

#### Exploratory analyses

To supplement the individual analyses, a pooled estimate of effect size will be calculated based on a random effects approach. A statistical model will be developed in which it is assumed that the size of the effect will not be the same for each behaviour but that the effect size varies randomly about some overall mean. Also, while the trial is designed and powered to detect changes in clinical behaviour, to inform future interventions, we will explore whether changes in clinical behaviour are related to changes in patient intention, self-efficacy and behaviour as well as changes in patient physiological outcomes (blood pressure, HbA1c).

#### Process evaluation analyses

Quantitative: We will use analytical methods we have previously developed to test for differences between groups on hypothesised targeted constructs, controlling for baseline differences [38]. Mediation models will be used to test whether intervention effects on behaviour are mediated through the targeted theoretical constructs, incorporating both sequential reflective and parallel impulsive processes.

Qualitative: Perceived intrapersonal, interpersonal, and contextual barriers and facilitators to engaging with the intervention will be coded using a coding framework and framework analysis informed by the Theoretical Domains Framework [43].

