#### Step three: patient recruitment

From our previous study [9], we identified that advising behaviours are not consistently recorded in patient notes. We therefore conducted a patient survey to ask patients to report on whether they had received this care in the past year. Consistent with this approach, we will invite a random sample of 100 patients with type 2 diabetes from each practice to complete an anonymous postal questionnaire 12 months after the delivery of the intervention. Patients with type 2 diabetes will be randomly selected from practice lists by the study contact in each recruited practice using a random sequence provided by the study statistician. Patients will be anonymous to the research team.

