### Process evaluation

#### Quantitative

To understand the intervention’s mechanism of change, we will survey participating clinicians in both groups prior to intervention delivery and again 12 months later to measure theoretical constructs targeted by our intervention and changes in these constructs associated with the intervention [38]. We will assess constructs based on models and measures from the iQuaD study including constructs from social cognitive theory (intention, self-efficacy, outcome expectancies), volitional constructs (action planning, coping planning) and behavioural automaticity for each of the six targeted clinical behaviours. In addition, we will also investigate whether the intervention alters perceptions of goal facilitation, goal conflict and goal priority between clinical behaviours based on recently developed short measures [29], as well as measures of clinicians’ time usage. Finally, given the team-based nature of primary care diabetes management we will explore whether the intervention alters any perceptions of team climate (participation, support for innovation, vision, and task orientation).

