### Outcome measures (computer read codes from patient electronic records)

#### Prescribing behaviours and foot examination

The behaviours relating to prescribing (prescribing additional antihypertensive drugs, prescribing additional therapy for managing glycaemic control) and foot examination are measured by extracting clinical and prescribing data from general practice computers using electronic queries developed and used in our previous study. We will study both the performance of clinical behaviours (measuring HbA1c, BP, foot checks) and the associated biochemical/physiological measurement (level of HbA1c; level of BP), accepting that there will be variability in the latter measures reflecting patient physiology and health behaviour. The data will relate to the 12-month period following intervention delivery and be extracted after month 12. Data will be extracted for a 24-month period (*i.e.*, 12 months prior to and 12 months after the month within which the intervention is delivered). We will thus account for any seasonal effects in performance of the target behaviours. The search queries will be sent to each practice, with written guidelines for how to run the query. For all registered patients with diabetes the research nurses will run computer queries to extract data on the total number of patients with diabetes in the practice and the number who have had: a foot check; blood pressure, HbA1c, and weight measured; level of systolic and diastolic blood pressure, level of HbA1c, cholesterol and body mass index; and diabetes-related medication (hypoglycaemic drugs, weight reducing drugs). We will pilot the data extraction procedure with an experienced NHS performance data manager to ensure reliability in data extraction.

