### Process measures (clinician questionnaire)

We will post a baseline questionnaire prior to delivery of the intervention and a 12-month follow-up questionnaire to each identified practice contact for distribution to clinicians identified as involved in providing care to people with type 2 diabetes along with a postage paid return envelope. Two reminders will also be sent at baseline and follow-up to non-respondents to promote a higher response.

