### Analysis

#### Main trial analysis

Practice attributes will be described. The primary analysis will involve testing, for each behaviour, whether there is a difference between intervention and control in the proportion of patients in each practice for whom the behaviour was undertaken during the 12 months following the intervention delivery. Rates of behaviour in intervention and control practices will be compared using a multilevel regression model taking into account the clustering of patients within practices. Practice list size will be included as a covariate given its use as a stratification factor. We will also consider specialist diabetes clinic and onsite insulin prescription as covariates depending on bivariate correlations. For the two prescribing behaviours the rates at which patients received the behaviour prior to the intervention will also be included as covariates in the analysis. The main analysis will be ‘intention to treat’; practices randomised to receive the intervention will be compared with other practices. A secondary ‘as treated’ analysis will take into account the uptake of the intervention in each practice.

In the case that outcome is missing for individual patients if we have other relevant variables for those individuals we will impute missing values using the ‘across cluster random-effects logistic regression method’ described by Ma *et al.*[42]. In the case of missing clusters no imputation will be undertaken. The potential impact of missing clusters on the estimated impact of the intervention will be assessed using sensitivity analysis involving a range of assumptions about the performance of the missing clusters.

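### The constructs are measured after delivery only at month 12, as the behaviour window closes, so the mediation models can show association with behaviour but cannot test mechanism

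*Protocol article*

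**What the plan says.** **Construct schedule.** Under the quantitative part of the process evaluation, "we will survey participating clinicians in both groups prior to intervention delivery and again 12 months later to measure theoretical constructs" targeted by the intervention. These include intention, self-efficacy, action and coping planning, and automaticity. The section on process measures gives the same two mailings ("We will post a baseline questionnaire prior to delivery of the intervention and a 12-month follow-up questionnaire") and none in between.

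**Behaviour window.** The main trial analysis compares "the proportion of patients in each practice for whom the behaviour was undertaken during the 12 months following the intervention delivery". For prescribing and foot examination, "The data will relate to the 12-month period following intervention delivery and be extracted after month 12". For the three advising behaviours, patients are asked to "complete an anonymous postal questionnaire 12 months after the delivery of the intervention", following the previous study's approach of asking about care over the past year.

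**Use of the two together.** The process evaluation analyses plan a comparison of constructs between arms, controlling for baseline, and then: "Mediation models will be used to test whether intervention effects on behaviour are mediated through the targeted theoretical constructs". The abstract presents the process evaluation as showing whether the intervention worked in the way hypothesised, and the Discussion makes understanding of the mechanisms of change an aim of the trial.

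**The concern.** A mediation claim needs the mediator to come before the outcome. Here the only construct value that the intervention could have altered is recorded at the end of the period over which behaviour is counted. Twelve months of doing something more often can itself raise confidence in doing it and make it more automatic. An association between month-12 constructs and behaviour, given arm, is therefore expected under the logic model and also under the opposite direction of effect.

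Randomisation protects the effect of arm on constructs and the effect of arm on behaviour. It does not protect the link between construct and behaviour, on which mediation rests. Adjusting for baseline constructs does not help either, because the reverse path operates after baseline.

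At stake is what the trial may conclude about how the intervention works, and hence what later interventions would take from it. The primary effect estimates are not at stake.

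**Working it through.** **1. Time order, from the protocol.**

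| Quantity | When | Section |
|---|---|---|
| Constructs, first measure | Before delivery | Process evaluation, Quantitative |
| Behaviour, records | Months 1 to 12 | Prescribing behaviours and foot examination |
| Behaviour, advising | Survey at month 12, looking back | Step three: patient recruitment |
| Constructs, second measure | Month 12 | Process evaluation, Quantitative; Process measures |

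Nothing else fills the gap. The feedback forms and facilitator checklists under Fidelity analysis are not said to measure the constructs, and the receipt and enactment questionnaires go out with the post-intervention process questionnaire. The clinician survey listed in Table 2 as a secondary source for behaviour is also at 12 months, so it is concurrent at best.

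**2. What reverse causation alone would produce.** The protocol gives no figure for mediation, so there is none to reproduce, and no correlation between construct and behaviour. The values of r below are assumptions. Let X be arm, Y behaviour and M the month-12 construct, with no path from M to Y:

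- Y = cX + e and M = gY + u
- Effect of arm on construct: a = gc
- Slope of behaviour on construct, given arm: b = g·Var(e) / (g²·Var(e) + Var(u))
- Apparent mediated share: ab/c = g²·Var(e) / (g²·Var(e) + Var(u)) = r², where r is the partial correlation of M and Y given X

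At r = 0.3 the share is 0.3² = 9%. At r = 0.5 it is 0.5² = 25%. The true share is 0 in both cases.

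**3. Does baseline adjustment help?** Simulated trials had 44 practices, a direct effect of 1 SD on behaviour and no path from construct to behaviour. The month-12 construct was 0.5 × baseline construct + s × behaviour + noise of SD 0.8. Both regressions were adjusted for the baseline construct, with 4,000 trials per setting. Mediation was declared when both paths were significant.

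| Reverse slope s | Mediation falsely declared | Apparent indirect effect (direct effect 1) | s² / (s² + 0.8²) |
|---|---|---|---|
| 0 | 0.3% | 0.00 | 0 |
| 0.3 | 13% | 0.12 | 0.09/0.73 = 0.12 |
| 0.5 | 38% | 0.28 | 0.25/0.89 = 0.28 |
| 0.8 | 62% | 0.50 | 0.64/1.28 = 0.50 |

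The last column is the formula of step 2 applied to this model, and it agrees with the simulation. Baseline adjustment leaves the false signal in place.

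**The case against.** **The article gives mediation one sentence, and the detail belongs elsewhere.** The choice of model may well be set out in a fuller plan. The measurement schedule, however, is fixed in the article, and no model recovers a time order that was not observed.

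**The constructs may have changed at delivery and persisted.** This stands. The month-12 value may reflect an early change, in which case the models would be picking up the hypothesised mechanism. A reader might infer that the trial reverses the order used in iQuaD, where constructs came first and behaviour was followed for 12 months. The documents do not support that: the pre-delivery constructs here still precede the behaviour, and the month-12 constructs are concurrent with the end of the window. Direction is ambiguous, not shown to be reversed.

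**The figures are illustrative.** This also stands. They put all of the association down to reverse causation, which is the extreme case. They also use a single-level model, although constructs belong to clinicians and outcomes to patients within practices.

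**Leaving out a mid-window questionnaire protects the trial.** This is a good argument. The protocol holds its post-delivery interviews until outcome data are in, because they might act as a prompt. A construct questionnaire part-way through could do the same to clinicians in both arms, including controls, who otherwise receive no session. A reader might think that such a mailing would leave the primary analysis untouched; since it would fall inside the primary outcome window, that cannot be assumed. It would also help only behaviours with dated record data. A monthly series is planned for the two prescribing behaviours, while advising rests on one survey at 12 months.

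**It is an additional analysis.** True. No primary estimate and no part of the two-of-six criterion for a positive trial depends on it.

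**Conclusion.** The point holds as a limit on interpretation. With constructs measured only before delivery and at month 12, and behaviour counted between those times, the planned models cannot tell constructs driving behaviour from behaviour driving constructs. They therefore cannot serve as a test of mechanism.

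The size of any error is not known from the documents. Under assumed correlations, with no true mediation and purely reverse causation, the spurious share is 9% at r = 0.3 and 25% at r = 0.5. These are illustrations of what the design cannot exclude. A reader might go further and infer that a positive mediation result would be false, or that the logic model is wrong; nothing in the protocol supports either.

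The baseline-adjusted comparison of constructs between arms remains a valid randomised comparison. It shows whether the intervention moved the constructs, by whatever route.

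**What to change.** Amend the quantitative paragraph of the process evaluation analyses to say, in substance:

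*Models relating month-12 constructs to behaviour over the preceding 12 months will be reported as associations consistent with the logic model. Because the two are measured over the same period, they are not a test of mechanism. The quantitative process result is the comparison of constructs between arms, adjusted for baseline.*

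Statements about mechanism in the trial report should keep to the same limit.

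This changes wording only. No analysis is dropped, no data collection is added, and the primary outcomes are unaffected. The price is a narrower claim about how the intervention works. A mid-window construct mailing is not recommended as a cheap alternative, for the reasons given under the objection.

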#### Fidelity analysis

Relevant portions of the recordings will be transcribed and analysed using a checklist of BCTs developed from the intervention protocol, to code whether the planned BCTs were actually delivered and whether the duration of delivery of each BCT changes over the course of the delivery period and between intervention facilitators. We will also distribute post-intervention feedback forms. Receipt of the intervention and enactment of targeted behaviours will be assessed through brief questionnaires delivered together with the post-intervention process evaluation questionnaire. We will also assess post-delivery facilitator debrief checklists of BCTs presumed to be delivered. Analyses will be descriptive and we will assess inter-rater reliability of BCT coding.

#### Cost analysis

A post trial economic analysis will estimate the costs of the intervention and cost of service use. Costs to populate the model will be based upon questionnaire responses from practices and patients and will be supplemented with secondary data such as the British National Formulary for medication costs where appropriate. Both probabilistic (to explore the impact of statistical imprecision) and deterministic (to explore other uncertainties and scenarios) will be estimated. Propensity score matching using parametric modelling techniques will be used to explore differences in average cost per patient of prescribing in relation to hypertension and glycaemic control between the intervention and control group.

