## Methods

### Trial design

The study will be a cluster randomised controlled trial with the general practice as the unit of randomisation and analysis to protect against contamination and given the level at which the primary outcome will be measured. The intervention will be a multi-level intervention, delivered to teams but targeting individual-level variables (see CONSORT checklist in Additional file 1).

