### Economic evaluation

The economic evaluation will comprise a cost analysis. All costs will be expressed in 2012/2013 values. The costs of delivering the intervention will be collected. Two main sources will be used to assign costs to healthcare resources [39,40] supplemented when necessary with unit cost data from other official sources and local surveys. Drug costs will be taken from the British National Formulary [41]. Within the trial a questionnaire at 12-month follow-up of an anonymous random sample of 100 patients from each practice will be asked to report on the use of NHS (National Health Service) services and medications over a twelve-month period. No discounting will be applied. A simplifying assumption will be made that the use of all costs and resources occurred at the beginning of the period. Specifically, the economic evaluation will involve the following:

1. Assessment of the costs of delivering the intervention in terms of staff training costs (both facilitator costs and GP time used in training) and any increase in the amount of standard patient education leaflets used by practices.

2. The average cost per patient to the NHS of medications prescribed in relation to hypertension, glycaemic control, and weight control. Conditional on available data, typical medication costs/usage across the intervention group will be compared to the general population. Differences between control and intervention groups will also be explored.

3. Costs of service usage: using self-reported questionnaires at 12 months from an anonymous sample of patients with type 2 diabetes from each participating practice, we will seek information on the use and NHS cost of community based weight control interventions. We will also seek to use practice records to assess the annual use of diabetes related services within practices. We will explore the use of comparator data that would allow us to forecast the additional workload that a practice would face as a result of successfully changing clinical behaviour and any induced change in patient uptake of practice based diabetes related services. Intervention and control groups will be compared, additionally national level data on service use by diabetes patients will be utilised for an additional comparator group.

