### Randomisation: sequence generation

The unit of randomisation will be the general practice: Randomisation will be performed by a statistician independent of the study team, using computer-generated random permuted blocks and will be stratified by practice size (the only organisation characteristic found to be related to performance in our previous study, iQuaD).

Random sample of 100 patients within clusters: The study statistician will provide each practice with a computer-generated list of random numbers to use for selecting which patients with type 2 diabetes to send a survey from their practice diabetes register.

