### Randomisation: type

Permuted-block randomisation, with practice list size as the blocking factor; 22 practices will be randomised to intervention, and 22 to control. The size of the permuted blocks will vary randomly.

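### The only method named for comparing prescribing cost between the randomised arms is propensity score matching, which randomisation makes unnecessary and which is not tied to the trial's clustered intention-to-treat analysis

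*Protocol article*

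**What the plan says.** The Cost analysis section of the protocol article names one method for comparing costs between arms: "Propensity score matching using parametric modelling techniques will be used to explore differences in average cost per patient of prescribing", and the sentence continues "in relation to hypertension and glycaemic control between the intervention and control group". The Economic evaluation section, on average medication cost per patient, adds "Differences between control and intervention groups will also be explored" and also says that the arms will be compared on service use. It names no method for either.

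The two groups are formed by randomisation. Under Randomisation: sequence generation, "The unit of randomisation will be the general practice", and under Randomisation: type, "22 practices will be randomised to intervention, and 22 to control", with practice list size as the stratifying factor. The Trial design section describes a "cluster randomised controlled trial with the general practice as the unit of randomisation and analysis".

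For the six clinical behaviours, the Main trial analysis section fixes a different approach. Rates are "compared using a multilevel regression model taking into account the clustering of patients within practices", list size is a covariate, and "The main analysis will be ‘intention to treat’; practices randomised to receive the intervention will be compared with other practices".

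**The concern.** Propensity score matching is built for groups that were not formed at random. Here allocation was random by practice, so each patient's chance of being in the intervention arm is set by the design. Among all randomised patients, a fitted score can therefore capture only chance imbalance. Covariates in a regression deal with that without leaving the randomised set.

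Two consequences could follow:

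- **Population.** Many forms of matching keep only patients who find a match. The cost difference would then describe a subset that need not be the intention-to-treat population for which the behaviour results are reported.
- **Clustering.** A matched comparison does not by itself reflect that whole practices were allocated. If patients were treated as independent, the standard error would be too small.

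Costs are part of the stated aim and are a numbered objective, and the Discussion says the cost analysis will inform scalability. A prescribing-cost difference from a comparison that is not aligned with the design would weaken that use.

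**Working it through.** **1. What is fixed and what is open.** Side by side, the two analysis sections read as follows.

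| Feature | Clinical behaviours (Main trial analysis) | Prescribing cost by arm (Cost analysis) |
|---|---|---|
| Method | Multilevel regression | Propensity score matching with parametric modelling |
| Analysis set | Intention to treat | Not stated |
| Practice clustering | Modelled | Not stated |
| List size | Covariate | Not stated |
| Status | Primary | Exploratory |

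The method in the right-hand column is a positive choice, not a gap. It is also the only method that the article names for any between-arm cost comparison.

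**2. The plan's own figures.** The protocol gives no figure for the cost comparison. Its Sample size section uses an intra-cluster correlation (ICC) of 0.06 for the behaviours, with 20 patients per practice as the conservative size and 40 as the anticipated size. To confirm that these inputs are read correctly:

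- 42.5% against 57.5%, 80% power, two-sided 5%, with continuity correction, needs 187 per arm.
- The design effect at 20 per practice is 1 + 19 × 0.06 = 2.14.
- 187 × 2.14 × 2 / 20 = 40.0 practices, as stated.
- The same method gives power of 80.1%, 84.0%, 89.4% and 92.1% for 40 × 20, 44 × 20, 40 × 40 and 44 × 40 (practices × patients). The protocol states 80%, 83.9%, 89% and 92%.

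**3. What ignoring practice would do.** Assume that matched patients are analysed without a practice effect and that costs have some ICC. With m patients per practice, the design effect is DE = 1 + (m − 1) × ICC, and the true size of a nominal 5% test is 2 × [1 − Φ(1.96 / √DE)].

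| ICC for costs (assumed) | m | DE | √DE | True type I error |
|---|---|---|---|---|
| 0.06 | 20 | 2.14 | 1.46 | 18% |
| 0.06 | 40 | 3.34 | 1.83 | 28% |
| 0.01 | 40 | 1.39 | 1.18 | 10% |
| 0.10 | 40 | 4.90 | 2.21 | 38% |

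The column √DE is the factor by which the standard error would be too small.

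**4. What losing patients would do to precision.** Suppose that matching kept 70% of 40 patients per practice (assumed), with 22 practices per arm and ICC 0.06. The effective number per arm falls from 22 × 40 / 3.34 = 263.5 to 22 × 28 / (1 + 27 × 0.06) = 235.1. Once clustering is allowed for, the standard error rises by √(263.5 / 235.1) = 1.06, about 6%. Precision is therefore a minor issue. What matters more is which patients the estimate describes and whether practice is in the model.

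**The case against.** The strongest reply is that the text is brief and exploratory, and that a stronger reading goes beyond it. Four inferences are tempting, and the document does not support them.

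- **That all cost comparisons rest on matching.** The sentence covers prescribing cost for hypertension and glycaemic control only. Delivery costs, weight-control medication and service use are outside it.
- **That matching replaces the randomised comparison.** The Economic evaluation section still says that arm differences will be explored, and nothing rules out an unmatched comparison. What can be said is that no method for one is named.
- **That patients will be discarded.** The unit and variant of matching are not stated, and some variants keep most or all patients.
- **That the standard errors will be wrong.** Clustered standard errors can be used after matching, and an article commonly leaves that detail to the full analysis plan. The error rates above are conditional, not a property of the plan as written.

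These limits all stand. They narrow the point but do not defend the choice of method.

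A further argument is non-response. Costs are drawn partly from an anonymous survey at 12 months, and in the previous study a mean of 41 of 100 invited patients per practice replied. The practice contact who draws the sample may also know the allocation. Responders could therefore differ between arms, which is a fair reason to adjust for covariates. The protocol does not give that reason, however. Matching does not bring back non-responders, and regression can make the same adjustment while keeping all responders and the practice structure.

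**Conclusion.** The point holds in a limited form. For one exploratory comparison, of hypertension and glycaemic prescribing cost per patient between randomised arms, the protocol names only an observational matching method. It gives no justification and makes no link to the clustered intention-to-treat framework that it sets out elsewhere. A better method is already in the protocol and costs little to carry over, so the wording should be changed.

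Its size depends on how the matched data would be analysed. If practice were ignored and the behavioural ICC of 0.06 also applied to costs, the type I error would be about 18% at 20 patients per practice and 28% at 40. At 40 per practice it would run from about 10% to 38% for an ICC between 0.01 and 0.10. If practice were properly accounted for after matching, this inflation would not arise. What would remain is an unnecessary method and a possible shift to a matched subset.

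The primary outcomes and the conclusion on effectiveness are not affected.

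**What to change.** Reword the Cost analysis section so that the arm comparison of prescribing cost is:

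- by intention to treat, in all patients with cost data;
- a cluster-adjusted regression suited to skewed costs (multilevel or GEE), with practice as the cluster;
- adjusted for practice list size, as in the main analysis;
- adjusted also for pre-intervention prescribing cost, if costs can be built from the 24-month record extraction described under the computer-record outcome measures. The patient survey is anonymous and taken only at 12 months, so it cannot supply a baseline.

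Keep propensity score matching, if wanted, only as a labelled sensitivity analysis or for the non-randomised comparison with general-population or national data mentioned under Economic evaluation.

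The cost is a change of wording. The core change needs no new data: survey questionnaires carry a practice code and records are extracted by practice, so practice can enter the model. Only the baseline-cost adjustment depends on which source is used for costs.
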